## Abbreviations

1. SMART/Sequential, multiple assignment, randomized trial
2. cDTR/Causality-driven dynamic treatment regime
3. MCI/Mild cognitive impairment
4. CT/Cognitive training
5. VRTC/Virtual reality Taichi
6. OffTC/Offline Taichi
7. SHAP/Shapley Additive explanations
8. SAC/Soft Actor-Critic
9. PI/Principal investigator

## Objectives

Mild cognitive impairment (MCI) represents a critical window for dementia prevention, yet current clinical guidelines lack specific guidance for individualized interventions despite substantial heterogeneity in treatment responses. This study uses a sequential, multiple assignment, randomized trial (SMART) design to identify optimal adaptive intervention strategies for older individuals with MCI using a causality-driven dynamic treatment regime framework (cDTR-SMART).

The chronic and relapsing nature of cognitive decline makes MCI uniquely suited to this methodology. It incorporates stepping therapy up for those who do not fully respond to initial intervention with intensified interventions, a tactic successfully applied to a number of complex chronic problems but not formally tested for MCI. The study will also examine how individual characteristics influence treatment effectiveness to enable personalized intervention strategies.

## Background

The increased life expectancy is one of the greatest achievements of global health systems. However, this increase has led to a substantial rise in age-related neurological disorders, particularly Alzheimer's disease and other dementias, necessitating health policies to focus[1], not only on survival but also on minimising health loss due to disability by promoting function and independence[2]. By 2021, dementia ranked as one of the top ten neurological conditions globally, with particularly high burden in people aged 80 years and older, second only to stroke. Between 1990 and 2021, the disability-adjusted life-years (DALYs) attributed to dementia increased by 168·7% (95% UI 156·3-179·9), driven by population ageing[3]. MCI represents a clinically subtle yet critical transitional state between normal ageing and dementia.[4] Despite its insidious onset and often unrecognized early symptoms, MCI carries significant prognostic implications, with 10-15% of affected individuals progressing to dementia annually—a risk 3·3 times higher than that of the general elderly population[5]. Therefore, MCI represents a critical window for dementia prevention and intervention, with early identification and intervention being essential for reducing dementia incidence.

In China, which has the world's largest ageing population with 280 million people aged 60 years or older (19·8% of total population) at the end of 2022, this demographic transition presents unprecedented challenges for dementia care delivery[6]. The prevalence of MCI among adults aged 60 years and older is 15·5%, affecting approximately 38·77 million individuals (95% CI 37·95-39·62), with higher rates observed in women and rural areas[7]. Research suggests that delaying dementia onset or progression by one year could reduce dementia cases by 9·2 million by 2050[7].

Evidence suggests that the optimal sequence and dose of interventions vary among individuals, with substantial heterogeneity in treatment responses[8]. Current clinical guidelines and expert consensus across different countries provide only broad, population-level recommendations for MCI and dementia prevention, lacking specific guidance for individualization in community and clinical practice[1,9–11]. Although clinicians typically adjust therapeutic strategies based on patients' conditions and treatment responses, the subtle onset and progression of MCI poses challenges for precise intervention matching[12]. Suboptimal intervention timing or inappropriate strategy selection might reduce treatment adherence and compromise the critical intervention window[13]. To address these challenges, we proposed an optimal adaptive intervention framework based on causal dynamic treatment regimes. Using a sequential, multiple assignment, randomised trial design, we identified an optimal adaptive intervention strategy specifically tailored for the community elderly population.

SMART designs often involve restricted participant populations under controlled conditions, making it challenging to extrapolate optimal intervention intensities to diverse real-world settings. This external validity concern is particularly relevant for MCI interventions, where population heterogeneity and varying environmental factors significantly influence treatment responses. To address these limitations, causal discovery methods offer potential improvements in model generalizability by explicitly accounting for underlying causal mechanisms that drive intervention effectiveness across different populations. Furthermore, conventional Dynamic Treatment Regimes (DTR) using Q-learning algorithms face methodological challenges in optimizing dual-task interventions common in cognitive rehabilitation. The approach struggles to capture non-linear interactions between different intervention intensities, potentially missing optimal combinations that could maximize therapeutic benefit. The complexity of cognitive and behavioural interventions for MCI necessitates more sophisticated approaches that can handle such non-linear relationships while maintaining interpretability for clinical implementation.

This methodological gap prompted our development of a causality-driven deep reinforcement learning framework that can effectively compute personalized intervention intensities for dual-task interventions while accounting for individual patient characteristics and temporal dynamics.

### Evidence before this study

Dementia is one of the leading causes of dependency and disability among older adults worldwide, affecting more than 57 million people with associated global healthcare costs[14]. The number of people with dementia is projected to increase nearly threefold to 153 million by 2050, with particularly concerning impact in China due to rapid population aging. Mild cognitive impairment (MCI) is a transitional state between normal aging and dementia, affecting approximately 38.77 million Chinese adults aged 60 years and older, with 10-15% progressing to dementia annually[11,15]. Early intervention in MCI stage is critical for delaying progression to dementia. Key interventions include cognitive stimulation, physical activity, vascular risk management, and addressing modifiable lifestyle factors such as diet, smoking cessation, and social engagement[1,16,17]. Despite the well-documented physiological and health benefits of physical exercise, the evidence supporting its impact on cognitive function remains controversial. We searched PubMed, Web of Science, and PsychInfo databases for randomized controlled trials published between database inception and April 1, 2024, focusing on long-term (≥12 months) physical exercise or multidomain interventions in non-demented, community-dwelling older adults. Previous meta-analyses examining exercise interventions have shown inconsistent results, with some reporting moderate positive effects on cognitive function in older adults, while others found negligible or no effects after accounting for publication bias and methodological limitations. Recent systematic reviews suggest that sustained multidomain interventions incorporating physical exercise may be more beneficial than exercise alone in preventing cognitive decline[18–26], particularly in individuals at high risk of dementia. Recent evidence indicates that interventions demonstrate a clear dosage-effect relationship, with optimal benefits occurring at specific thresholds that vary by individual characteristics such as age and cognitive status[27]. However, current clinical guidelines and expert consensuses across countries provide only broad intervention recommendations, lacking specificity and practical operability for clinical implementation[11]. The optimal type and duration of exercise for potentially preventing cognitive decline or dementia onset remains unclear, with considerable variation in exercise protocols observed across studies. Therefore, developing analytical frameworks to determine optimal intervention strategies and their implementation represents a critical gap in current research. Additionally, the comparative effectiveness of single-domain exercise interventions versus comprehensive multidomain approaches in preserving cognitive function and reducing dementia risk has not been systematically evaluated in long-term trials. More importantly, research specifically examining optimal adaptive intervention frameworks on MCI remains none, with most studies using fixed intervention protocols rather than dynamic, personalized approaches.

### Added value of this study

This study represents the first exploration of adaptive optimal intervention strategies in MCI management through a causality-driven dynamic treatment regime framework by sequential, multiple assignment, randomized trial (cDTR-SMART). The cDTR-SMART is a generalizable computational framework for deriving adaptive optimal intervention strategies, which integrates Peter-Clark causal discovery algorithms to identify influential causal pathways and incorporates them into a state space model, ultimately utilizing reinforcement learning to determine optimal action spaces across different states.

In our analysis of participants, we identified cognitive status, age, and presence of diabetes and hypertension as key state space variables, which enabled the derivation of personalized optimal intervention combinations (Virtual reality Taichi, Offline Taichi, Cognitive function training) through our reinforcement learning model. The study revealed substantial individual heterogeneity in treatment responses, with an average treatment effect of 0·587 (95% CI [0·022, 1·152]). Notably, the intervention demonstrated pronounced effectiveness in older participants with lower cognitive states (ITE: 0.94), with this effect further amplified in the presence of chronic conditions (ITE: 1.12), suggesting that the most vulnerable subgroups might benefit most from the intervention. Additionally, SHAP analysis revealed that age demonstrated the most pronounced heterogeneous effects in VR Taichi responses, while diabetes status showed consistently positive clustering of SHAP values for offline Taichi practice, indicating enhanced benefits for participants with metabolic conditions. This data-driven approach transcends the generic non-pharmacological intervention guidelines in current dementia prevention protocols by providing actionable, precise intervention recommendations. Furthermore, by incorporating causal discovery methods, this approach offers interpretable insights into intervention intensity adjustments based on individual patient characteristics, making it both practically applicable and theoretically sound for personalized cognitive intervention.

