## Secondary Aim

Evaluate the average treatment effects (ATE) of different intervention modalities (virtual reality Taichi, offline Taichi, and cognitive training) on cognitive scores measured by Memory Guard.

Analyze heterogeneity in treatment effects across participant subgroups based on cognitive status, comorbidities, and demographic characteristics.

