## Procedures Involved

This study employs a prospective sequential, multiple assignment, randomized trial design. The 24-week SMART design comprises two 12-week phases. In the first phase, eligible participants will be randomly assigned to receive either offline Taichi plus cognitive training (OffTC+CT) or virtual reality Taichi plus cognitive training (VRTC+CT). Each intervention will consist of 1-hour weekly exercise combined with 1 hour weekly cognitive training.

At week 12, participants will be assessed for intervention mastery, with non-responders (defined as those subjectively unable to master the intervention content, scoring less than 3 on a 5-point Likert scale) being re-randomized to alternative or intensified interventions for the second 12-week phase. Responders in Group OffTC+CT will continue their original intervention protocol, while non-responders will be randomly assigned to either VRTC+CT or doubled doses of their original intervention (2OffTC+2CT). Similarly, responders in Group VRTC+CT will maintain their initial protocol, while non-responders will be randomly assigned to either OffTC+CT or doubled doses of their original intervention (2VRTC+2CT). The control group will receive only health education and routine care throughout the 24-week period.

The anticipated duration for individual participation in the study is 24 weeks (6 months). The duration anticipated to enroll all study participants is approximately 9 months (April to December 2023).

[figure not shown]

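### The protocol reports this study's own effect estimate, state variables and subgroup findings while listing them as planned, so this version alone cannot show prespecification, and its subgroup claims carry no measure of uncertainty

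*Protocol*

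**What the plan says.** **As results.** Added value of this study attributes the following to the present study, in the past tense:

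- State variables: "we identified cognitive status, age, and presence of diabetes and hypertension as key state space variables".
- Overall effect: "The study revealed substantial individual heterogeneity in treatment responses, with an average treatment effect of 0·587 (95% CI [0·022, 1·152" (the quote stops just before the closing brackets).
- Subgroups: "pronounced effectiveness in older participants with lower cognitive states (ITE: 0.94" and then "with this effect further amplified in the presence of chronic conditions (ITE: 1.12". The same paragraph concludes that the most vulnerable may gain most, and adds SHAP findings by age and diabetes.

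Background says that an optimal adaptive strategy has been identified. Implications of all the available evidence refers to a decision tree already derived and draws conclusions for practice.

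**As plan.** Primary Aim and Primary Outcome make the derived strategy the target of the trial. Secondary Outcomes lists the average treatment effect on Memory Guard scores and individual effects across subgroups. Secondary Aim reads: "Analyze heterogeneity in treatment effects across participant subgroups based on cognitive status, comorbidities, and demographic characteristics". Statistical Considerations describes the average-effect and heterogeneity analyses in the future tense.

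**Dates.** Procedures Involved anticipates enrolment over "approximately 9 months (April to December 2023" and 24 weeks of participation. Evidence before this study describes a literature search of trials "published between database inception and April 1, 2024". The References include a publication of August 2024 and several access dates of 25 March 2025.

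**The concern.** A protocol lets a reader separate what was decided before the data from what was decided after. Here the primary outcome (the strategy) and both secondary outcomes (average effect, subgroup effects) appear once as findings and once as intentions, with nothing to say which came first. A reader could take the average effect, whose lower limit is 0.022, and the subgroup pattern as confirming a plan made in advance. This document gives no basis for that.

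The second issue is the strength of the subgroup statements. They are worded as findings about who benefits most, but they rest on two bare point estimates. The only interval nearby belongs to the overall average effect. If the statements are carried into practice guidance, as the Implications section does, the reader cannot tell how uncertain they are.

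**Working it through.** **1. Reported against planned**

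| Quantity | Reported as found | Listed as planned |
|---|---|---|
| Optimal strategy | Background; Implications (decision tree) | Primary Aim; Primary Outcome |
| Average treatment effect | Added value: 0.587 (0.022 to 1.152) | Secondary Aim; Secondary Outcomes; Statistical Considerations |
| Subgroup effects | Added value: 0.94 and 1.12; SHAP findings | Secondary Aim; Secondary Outcomes; Statistical Considerations |

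**2. Timing.** The latest planned enrolment is the end of December 2023. Adding 24 weeks (168 days) to 31 December 2023 gives 16 June 2024, so planned follow-up ends about mid-June 2024. The access dates of 25 March 2025 are some nine months later. This version was therefore completed after the planned end of data collection.

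**3. The stated interval.** Inputs: estimate 0.587, limits 0.022 and 1.152.

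- Midpoint = (0.022 + 1.152)/2 = 0.587, which reproduces the stated estimate.
- Half-width = (1.152 − 0.022)/2 = 0.565.
- SE = 0.565/1.96 = 0.288.
- z = 0.587/0.288 = 2.04; two-sided p = 0.042.

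**4. What the subgroup figures could support.** The protocol gives no subgroup sizes or intervals, so this step is illustrative. Assumptions: each figure is the mean effect in a subgroup holding a share f of the sample; the overall effect is the weighted average of the subgroup and its complement; variances are equal; and the two parts are independent.

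- Complement effect: c = (0.587 − f·s)/(1 − f), where s is the subgroup effect.
- SE of (s − c) = 0.288 × √(1/f + 1/(1 − f)).

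| s | f | c | s − c | SE | z | p |
|---|---|---|---|---|---|---|
| 0.94 | 10% | 0.548 | 0.392 | 0.961 | 0.41 | 0.68 |
| 0.94 | 25% | 0.469 | 0.471 | 0.666 | 0.71 | 0.48 |
| 0.94 | 50% | 0.234 | 0.706 | 0.577 | 1.22 | 0.22 |
| 1.12 | 10% | 0.528 | 0.592 | 0.961 | 0.62 | 0.54 |
| 1.12 | 25% | 0.409 | 0.711 | 0.666 | 1.07 | 0.29 |
| 1.12 | 50% | 0.054 | 1.066 | 0.577 | 1.85 | 0.064 |

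The formulas reduce to z = [(s − 0.587)/0.288] × √(f/(1 − f)). To reach 1.96, f would have to be about 72% for 0.94 and about 53% for 1.12. Shares that large look unlikely for groups defined by older age and lower cognition together, and then also by chronic disease, but the protocol does not give the sizes.

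**The case against.** The strongest reply has five parts.

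- **An earlier plan may exist.** The SAP is not at hand, and a dated protocol version may precede the data. This stands. A reader might infer that the analyses were in fact devised after the results were seen, but the document does not show that. It shows only that this version is no evidence of the opposite.
- **The results may come from a pilot.** Addressing Heterogeneity in Treatment Response mentions preliminary data. This is possible but is the weaker reading, because Added value attributes the figures to the present study and calls it the first exploration of its kind. The sponsor can settle it in one sentence.
- **The planned subgroup factors need not come from the data.** This stands. Secondary Aim names only broad classes, Statistical Considerations names no specific factors, and Evidence before this study cites published variation by age and cognitive status. It cannot be said that the data picked them.
- **The April 2024 search date proves little.** This stands. It precedes the last planned follow-up visit. The timing argument rests on the 2025 access dates.
- **Nothing is labelled confirmatory.** This is true: the protocol uses exploratory and data-driven language, the average effect is a secondary outcome, and the only stated type I error belongs to the sample-size calculation. No stated error rate for the average effect can therefore be called understated. The conflict between reported and planned remains.

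A reader might also argue that 0.94 and 1.12 lie inside 0.022 to 1.152, so the protocol's own interval refutes heterogeneity. It does not. That interval describes the uncertainty of the overall mean effect, and a subgroup estimate falling inside it tests nothing in either direction.

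**Conclusion.** The point holds in two limited parts.

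First, this version mixes reported results with planned analyses for the primary and both secondary outcomes, and it was completed after the planned end of follow-up. On its own it cannot support a claim of prespecification. This rests on the text and its dates and needs no statistical assumption. It matters more because the average effect is borderline (z = 2.04, p = 0.042), although it has not been shown that any particular analytic choice would have changed that result.

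Second, the subgroup statements lack the support their wording implies: there is no interval, subgroup size or interaction test. For shares from 10% to 50%, the contrast with the complement gives z of 0.41 to 1.22 for the first figure and 0.62 to 1.85 for the second. These values depend on the assumed shares, equal variances and independence. They show that the claim is unsupported as reported, not that heterogeneity is absent.

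**What to change.** 1. Remove the results and practice conclusions from Background, Added value of this study and Implications of all the available evidence, or state whether they come from this trial or from a separate pilot.
2. Date this version against access to outcome data, and cite any protocol version or SAP locked earlier.
3. In the sections from Primary Aim to Secondary Outcomes and in Statistical Considerations, mark whatever was fixed after data access (state variables, subgroups, individual-effect contrasts) as post hoc and exploratory.
4. Wherever subgroup effects are reported, give subgroup-versus-complement contrasts with confidence intervals and subgroup sizes in place of bare point estimates.

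The work is rewording, a provenance statement and a few additional estimates, with no change to trial conduct. The price is weaker claims about the average effect and about who benefits most, unless an earlier locked plan can be produced.

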### Implications of all the available evidence

The mounting prevalence of dementia presents an urgent public health challenge that demands immediate attention. While current clinical guidelines acknowledge the importance of early intervention, they often lack specific, actionable recommendations for personalized treatment. Our study bridges this critical gap by providing evidence-based, optimal adaptive strategies through the innovative cDTR-SMART framework. Notably, our findings highlight the crucial role of comorbid chronic diseases in MCI intervention outcomes, demonstrating that incorporating these factors can significantly enhance treatment effectiveness. The decision tree model derived from our analysis offers practical, implementable guidance for community-based MCI prevention and management. Furthermore, the compatibility of our intervention framework with existing mobile health platforms enables real-time, precision-based adaptive interventions, making it particularly valuable for widespread community implementation. Beyond MCI, the cDTR-SMART framework represents a versatile methodology that could be adapted for developing personalized interventions across various chronic conditions, potentially transforming the approach to precision medicine in community healthcare settings.

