### Addressing Heterogeneity in Treatment Response

Mild cognitive impairment (MCI) patients demonstrate significant heterogeneity in disease progression, cognitive profiles, and responses to interventions[32]. Current evidence suggests that the optimal sequence and dosage of interventions vary substantially among individuals, with important implications for intervention effectiveness. The SMART design explicitly addresses this heterogeneity by enabling evaluation of multiple intervention pathways tailored to individual response patterns.

For example, as shown in our preliminary data, participants with different baseline cognitive statuses and comorbidity profiles respond differently to VR-based Taichi versus conventional Taichi. A SMART design allows us to systematically investigate these differential response patterns and develop evidence-based rules for matching patients to the most beneficial intervention sequences.

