## Secondary Outcomes

Average treatment effects (ATE) of cognitive scores measured by Memory Guard.

Individual treatment effects (ITEs) across participant subgroups with different baseline characteristics.

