## Statistical Considerations

**Average Treatment Effects**

We will use causal forests double machine learning to estimate:

Total ATE between treatment and control groups on cognitive outcomes

Component-specific ATE for VRTC, OffTC, and CT

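### The protocol says its findings demonstrate that using comorbidity significantly improves treatment, but the only comorbidity figures show who may benefit more, not that tailoring on comorbidity gains anything

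*Protocol*

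**What the plan says.** In the Protocol, section *Implications of all the available evidence*, the findings on comorbid chronic disease are described as "demonstrating that incorporating these factors can significantly enhance treatment effectiveness". The section then recommends the derived decision tree for community use.

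The figures are in *Added value of this study*. The overall result is given "with an average treatment effect of 0·587 (95% CI [0·022, 1·152". The subgroup results are "pronounced effectiveness in older participants with lower cognitive states (ITE: 0.94" and, for the same effect, "with this effect further amplified in the presence of chronic conditions (ITE: 1.12". That section's own reading is hedged: it says only that the most vulnerable groups may be those who gain most. It adds, without a number, that "diabetes status showed consistently positive clustering of SHAP values for offline Taichi practice".

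Three other sections bear on the point:

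- *Addressing Heterogeneity in Treatment Response* sets the goal to "develop evidence-based rules for matching patients to the most beneficial intervention sequences". It also reports, from preliminary data and without figures, that participants with different comorbidity profiles differ in their response to VR versus conventional Taichi.
- *Secondary Outcomes* lists "Individual treatment effects (ITEs) across participant subgroups with different baseline characteristics" and names no comparator.
- *Statistical Considerations* defines "Total ATE between treatment and control groups on cognitive outcomes", plans component-specific effects for the three components, and plans a SHAP analysis of heterogeneity.

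**The concern.** Two different questions are run together. The first is who gains more from being treated, which is a subgroup effect of the intervention. The second is whether outcomes improve when comorbidity is used to decide how much of each component a person receives. That is the value of a tailored strategy against the same strategy without the factor.

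A characteristic can be a strong and precisely estimated modifier of the overall effect and still be useless for tailoring, because it moves every option by the same amount. Conversely, a characteristic that reverses which option is better can leave the overall effect unchanged. More precision on the first question therefore does not answer the second.

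The optimal adaptive strategy is the trial's primary aim. As worded, the protocol would have comorbidity reported as a demonstrated tailoring factor when its figures are compatible with no gain from tailoring on it.

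**Working it through.** **Inputs from the protocol.** ATE 0.587 (95% CI 0.022 to 1.152); subgroup effects 0.94 and 1.12; 54 required in the intervention group (27 per active arm), with about 30 per arm to be enrolled. Comorbidity prevalence is not given, so it is assumed below.

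**Step 1. Reproduce the stated figure.** The CI midpoint is (0.022 + 1.152)/2 = 0.587, which matches. SE = (1.152 − 0.022)/(2 × 1.96) = 0.288, and z = 0.587/0.288 = 2.04.

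**Step 2. What the subgroup figures imply for tailoring.** For illustration, take 0.94 and 1.12 as the average effects of two active options, weighted 1:1, in people without and with comorbidity, at an assumed 50% prevalence.

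- *Comorbidity shifts both options equally.* Both options have effect 0.94 without comorbidity and 1.12 with it. Any single option gives (0.94 + 1.12)/2 = 1.03, and so does the tailored rule. Gain: 0.
- *The better option flips by 0.2 each way.* Without comorbidity the options give 1.04 and 0.84; with it, 1.02 and 1.22. The single options give (1.04 + 1.02)/2 = 1.03 and (0.84 + 1.22)/2 = 1.03. The tailored rule gives (1.04 + 1.22)/2 = 1.13. Gain: 0.10.

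Both cases reproduce 0.94 and 1.12, so those figures cannot tell them apart. The 0.2 is illustrative and is not an estimate.

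**Step 3. Side check on the word *significantly*.** The raw difference is 1.12 − 0.94 = 0.18. If the ATE's precision is split over the whole sample with comorbid share q, the SE of a difference between groups is 0.288 × √(1/q + 1/(1 − q)):

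- q = 0.5: 0.288 × 2 = 0.58, so 0.18 is 0.31 SE.
- q = 0.3 or 0.7: 0.288 × 2.18 = 0.63, so 0.18 is 0.29 SE.

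The 0.94 may include comorbid participants. If so, the gap to those without comorbidity is 0.18/(1 − q): 0.26, 0.36 and 0.60 at q = 0.3, 0.5 and 0.7. These are 0.4, 0.6 and 0.95 SE. Both subgroup figures come from an older, low-cognition subset, so true precision is probably worse.

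**Step 4. Precision of the randomised contrast between active arms.** For VRTC+CT minus OffTC+CT by a binary characteristic with prevalence p and n per arm, the 95% half-width in SD units is 1.96 × √(2/(np) + 2/(n(1 − p))):

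- n = 30, p = 0.50: 1.96 × √0.267 = 1.01
- n = 30, p = 0.25: 1.96 × √0.356 = 1.17
- n = 27, p = 0.20: 1.96 × √0.463 = 1.33

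To put this on the ATE's scale, a simple 60-versus-30 comparison implies SD = 0.288/√(1/60 + 1/30) = 1.29. The half-widths are then about 1.01 × 1.29 = 1.3 to 1.33 × 1.29 = 1.7.

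**The case against.** The other side has several fair points.

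- **The basis of the claim is not stated.** The implications section refers to the findings generally. Personalisation is attributed to the reinforcement learning model, and the comparator of the individual effects is never given; treatment versus control is inferred from *Statistical Considerations*. A reader might infer that the whole personalisation conclusion rests on an active-versus-control contrast. The protocol does not establish that. What can be said is that 0.94 and 1.12 are the only quantified comorbidity support.
- **There is other evidence.** The SHAP remark and the preliminary statement on VR versus conventional Taichi are relevant, and the second is the right kind of contrast. Neither has a figure. A positive SHAP pattern for offline Taichi in diabetes does not show that it beats VR Taichi there, and responding differently need not mean that the best option changes. Entering diabetes and hypertension into the model does not show that they add value.
- **The strategy is not a two-way choice.** *Primary Outcome* describes time allocations in 5-minute intervals, and the second stage includes doubled doses. If comorbidity alters a dose-response, the best allocation can change without any VR/offline reversal. This stands. The zero gain in Step 2 needs all options to shift equally, and the week-12 contrast alone cannot validate the full strategy.
- **Modality-specific work is planned.** Component-specific effects and SHAP are named, so a reader should not conclude that a difference between the modalities would necessarily go unseen. Detailed interaction specifications may also sit in an analysis plan that is not at hand.
- **The section is an implications panel that fixes no analysis.** That is true, but it states a conclusion on the primary aim and leads straight to a recommendation for community use.

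**Conclusion.** The point holds in a limited form. The reported figures suggest possible effect modification and do not demonstrate a gain from tailoring on comorbidity. They fit a gain of 0 as well as a positive one (0.10 in the illustration), and the difference of 0.18 is about 0.3 SE under a favourable whole-sample assumption. The claim therefore goes further than the protocol's own hedged reading of the same numbers.

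The main conclusion is logical and does not depend on the assumed prevalence. The sizes do. They assume comorbid shares of 0.3 to 0.7 (Step 3) or 0.2 to 0.5 (Step 4), a simple two-group variance, and, in Step 2, that 0.94 is the value without comorbidity, which the protocol does not say.

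A reader might go further and infer that tailoring on comorbidity has been shown to be worthless. The document does not support that either, since it reports no comparison of strategies that would settle the matter in either direction.

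**What to change.** 1. **Reword the implications section.** Limit it to possible effect modification by comorbidity, in line with *Added value of this study*, and drop *demonstrating* and *significantly*.
2. **Add an exploratory contrast to *Statistical Considerations*.** Estimate VRTC+CT minus OffTC+CT at week 12, as randomised and before re-randomisation, by diabetes, hypertension, age and baseline cognition. Give interaction estimates with 95% CIs. Label active-versus-control subgroup effects as showing who benefits from intervention only.
3. **Base any tailoring claim on the value of the strategy.** Report the cross-validated or held-out difference in expected Memory Guard score between the strategy with and without diabetes and hypertension as inputs. Held-out evaluation is needed because the same difference computed on the training data is biased upward. Report it with its interval whatever the result; whether the interval includes 0 should not decide if it is shown.

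The cost is a modest amount of analysis on data the trial already plans to collect, plus rewording. The downside is that the intervals will be wide (Step 4) and the conclusion on personalisation becomes less favourable.
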